## Abstract

(1) Introduction: Dietary and lifestyle changes along with the cultural and linguistic barriers convert the immigrant women of Pakistani origin into a risk population for developing metabolic syndrome (MetS) and cardiovascular diseases (CVD). The objective of this project is to evaluate the efficacy of a culturally and linguistically appropriate food education program based on the Transtheoretical model that will allow the participants to become ambassadors of healthy eating habits for their community. (2) Methods: In this community-based RCT, any Pakistani adult woman with residence in Badalona and Santa Coloma de Gramenet will be able to participate. We will use a mixed model approach. From the quantitative perspective, the participants will answer a survey accompanied by a multilingual nutritionist that will help us to determine the sociodemographic, clinical, anthropometric, dietary data, and quality of life. From the qualitative perspective, we will conduct 6 focus groups (3 in each municipality) to determine the cultural and religious beliefs with the aim of tailoring the intervention to the target population. Hereafter, the participants from one municipality will randomly become the control group and from the other, the intervention group. The intervention group will participate in 10 weekly food education sessions based on the Transtheoretical model while the control group will receive 3 general educational sessions on food and health. During the evaluation procedure, we will assess the impact of the intervention considering the outcomes of the study. (3) Discussion: This study will establish intercultural bridges between health professionals and the Pakistani community living in Catalonia. The project will open the door for future interventions, and it will be sustainable in time as the participating women will become health promotion agents for the rest of their community.

## 1. Introduction

The number of Pakistani people living in Spain is rapidly increasing. According to the recent census data, between 2010 and 2020, the Pakistani population increased by approximately 72% [1]. Currently, 99.352 people of Pakistani origin are residing in Spain, of which 56% live in Catalonia, especially in Barcelona and its surroundings [1,2]. The group of women in this community are a minority (29%) [3] who mostly arrive in Catalonia due to the family reunification procedures predominantly sponsored by the male members of the family (husband or father) [4]. Due to cultural and linguistic barriers and difficulties in accessing the job market, immigrant women of Pakistani origin are currently one of the most invisible ethnic/racial groups in Catalonia [4]. Although the socio-demographic and socio-economic profile of the Pakistani population living in Catalonia is well known [2,3,4], the Catalan context does not have any information on its health and nutrition aspects. However, these data are available in countries with higher Pakistani populations such as Norway [5,6,7], the United Kingdom [8,9], the United States [10,11], and Australia [12].

Due to the similarity in the sociocultural and linguistic profiles [5], mostly the research in health and nutrition is conducted jointly for all the immigrant South Asian (SA) population, especially for those who proceed from India and Pakistan. It is well established that the migrant SA population tends to have a higher risk for the development of type 2 diabetes and cardiovascular disease (CVD) compared with the western population [13,14]. In such a way that the risk of developing type 2 diabetes is two to four times higher in SA as compared to Europeans [8,15,16]. They are also affected by CVD approximately a decade earlier than the Western population [17] as 25% of myocardial infarctions occur in SA under 40 years of age and more than 50% of deaths from CVD occur in SA under 50 years of age [18]. Furthermore, they have more body fat and less lean tissue than white people of European descent at any Body Mass Index (BMI) level [16,17]. SA also tends to have lower high-density lipoprotein (HDL), higher triglycerides, and increased lipoprotein (a) as compared to other ethnicities [16,17]. The prevalence of hypertension is also slightly higher in them [13]. The reunification of these factors is established as metabolic syndrome (MetS) [19]. Currently, the prevalence of MetS in SA immigrants is estimated to be 50% in the United States and 40% in the United Kingdom [19,20].

Apart from the genetic and metabolic factors, dietary and lifestyle changes caused by acculturation, account for the high prevalence of MetS in SA immigrants [5,16,17,20]. In addition to this, cultural and linguistic barriers make it difficult for them to participate in the standard health promotion programs [5,17,21]. Consequently, their health deteriorates throughout their stay in Western countries [22,23].

Different countries have successfully designed and implemented culturally and linguistically adapted health promotion programs to address this situation. A recent meta-analysis found a 35% of reduction in diabetes in SA immigrants who participate in culturally and linguistically appropriate lifestyle modification interventions [9].

In some countries, the prevalence of MetS and CVD is higher in SA women as compared to men [5,20,24]. However, this difference is more significant in immigrants of Pakistani origin [24,25]. In Norway, the risk of developing obesity and type 2 diabetes is higher in Pakistani women as compared to men [6,7,8,9,10,11,12,13,14,15,16,17,18,19,20,21,22,23,24,25]. Apart from being highly susceptible to these diseases, Pakistani women also tend to face more difficulties in integrating into the host country as compared to the men of the same origin [6,12]. They are also more affected by cultural and linguistic barriers, caused by acculturation stress and social isolation, is highly common among them [26]. Due to their physical, psychological, and socio-economic vulnerability, some countries have successfully designed and implemented culturally and linguistically appropriate food and lifestyle interventions targeting specifically immigrant women of Pakistani origin. Following this line, and taking into account all the key success factors mentioned by different authors who have conducted similar studies in other contexts [27], the current study aims to (a) evaluate the efficacy of a culturally and linguistically appropriate food education program based on the Transtheoretical Model of health behavior change [28] for Pakistani women living in Catalonia, and (b) empower the participating women to become the ambassadors of healthy eating habits in their community.

## 2. Materials and Methods

### 2.1. Study Design

The present study is community-based participatory research in which a RCT will be implemented. We will combine different methods to obtain and analyze both qualitative and quantitative data. The quantitative perspective will be used to determine the sociodemographic, health and life quality, anthropometric and dietary aspects. While the qualitative view will be used to obtain deeper information about health and nutrition beliefs and to adopt the intervention on the needs and knowledge of the target population.

### 2.2. Study Setting and Participants

This project is being carried out in the province of Barcelona, specifically in the region of Barcelonès, which is home to more than half of the foreign population of Pakistani origin residing in Catalonia [2]. Concretely, this study is taking place in Badalona and Santa Coloma de Gramenet which are two neighboring municipalities and, respectively, the second and fourth most populous in Catalonia by the Pakistani population [29].

Pakistani women living in these municipalities have the support of Fundació Ateneu Sant Roc (Badalona) and Casa Àsia (Santa Coloma de Gramenet), two institutions working with the same goal: the integration of migrant people into the host society and its environment. Both institutions accepted to participate and signed the consent form to participate in the research. Annually, Fundació Ateneu Sant Roc and Casa Asia attend between 50 to 60 Pakistani adult women. We have invited all of them and their close acquaintance to participate in the study. To facilitate the participation of Pakistani women in this community-based project we have set the inclusion and exclusion criteria as wide as possible (Table 1).

70 women associated with Casa Asia and 67 from Fundació Ateneu Sant Roc have accepted to become part of the study forming a sample of 137 women. There are three factors that indicate the homogeneity of the sample; firstly, the majority of the participants are in the process of learning Spanish and Catalan from the collaborating institutions, secondly, by belonging to the neighboring municipalities, their socioeconomic and sociodemographic conditions are similar and thirdly, all of them migrated between 2000 and 2022. So, to evade the contamination of information the participants from one institution will randomly become the control group and from the other, the intervention group.

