### 3.1. Phase 1: Dissemination and Recruitment

This phase corresponds to the dissemination of the project and the recruitment of participants for control and intervention groups. We organized introductory sessions with the educators and volunteers of the institutions, as well as their Pakistani users to present the project. Communication was realized in Urdu and Punjabi during the meetings with Pakistani women. Hereafter, the team of institutions and their users have helped us in the dissemination and recruitment procedure. We have also organized meetups at the different community spaces (social institutions, libraries, community centers, mosques, and female driving schools) to explain in-depth all the characteristics of the study to the interested women. In the end, we handed over to them the information sheets that sums up the principles of the study along with the informed consent. We also provided our contact and obtained the names, addresses, and contact numbers of those willing to participate in the project. We have completed this phase by forming a sample of 137 women.

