Empowerment: The implementation of the sessions in small groups will promote socialization and sorority among participants. We will highlight the impact of the eating habits of Pakistani women on their families and we will invite them to extend the role of healthy eating habits to the rest of the community.

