### 3.5. Evaluation

The protocol study will include a process and an impact evaluation that will take part at the end of health education sessions, in which we will collect the same variables that were gathered during the baseline data collection. The only modification will be the addition of an ad hoc satisfaction questionnaire to comprehend the linguistic, cultural, and content comprehension issues. We will also repeat the 6 focus groups in order to assess the changes in food and health beliefs and nutritional knowledge and skills. Photovoice technique will also help us to determine the improvement in the eating habits, and nutrition knowledge of participants. The evaluation procedure will be repeated at 3 and 6 months.

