**10. Photovoice**	1 h	- Recognize the representative dishes of Pakistani cuisine. - Understand the meaning of food for the Pakistani community.	- In this last session, the participating women will bring a photo of a healthy dish or snack made with ingredients that have a very important meaning for them. There will be an exhibition of the images, so that each participant will share the meaning of their dish with their fellows, explaining the modifications they have made to convert their dish into a healthy plate.	- In this session, the participants will be allowed to come accompanied by their family and friends. They will present them their plates as well.

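### Allocation by institution is the only stated guard against contamination, but the programme's outreach and open final session work against it before the 3- and 6-month evaluations

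*Protocol article*

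**What the plan says.** **Safeguard.** Section 2.2 allocates whole institutions so that "to evade the contamination of information the participants from one institution will randomly become the control group", with the other institution forming the intervention group. The sample is 137: "70 women associated with Casa Asia and 67 from Fundació Ateneu Sant Roc have accepted". The institutions serve "two neighboring municipalities". On recruitment, 2.2 says "We have invited all of them and their close acquaintance to participate in the study", and 3.1 adds meetings in shared community venues such as mosques and driving schools.

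**Outreach.** Making participants ambassadors is aim (b) in the Introduction. Under Empowerment, section 3.4 points to women's influence on their families and then says "we will invite them to extend the role of healthy eating habits to the rest of the community". In Table 2, the maintenance stage includes taking on a health-promotion role for other Pakistani residents, with no municipality named. In Table 3, session 10 is open: "the participants will be allowed to come accompanied by their family and friends". Several earlier sessions hand out an infographic, booklets or a recipe book.

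**Evaluation.** Section 3.5 collects the baseline variables again at the end of the sessions and names a satisfaction questionnaire as the sole change to them. It adds repeat focus groups and photovoice, and then says "The evaluation procedure will be repeated at 3 and 6 months".

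**The concern.** Separate institutions keep women of different arms out of the same teaching room. They do not stop information travelling afterwards, and here the programme encourages it to travel. The efficacy aim needs the control group to remain unexposed to the 10-session programme until its last evaluation. The ambassador aim asks intervention women to pass the content on, and nothing in the article keeps the two apart by place, by time or by who may attend.

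At stake is how the 3- and 6-month results can be read. Spread to control women would shrink the difference between arms, and would shrink it more the better the ambassador aim succeeds. If control scores then rose, the investigators would have no record of whether the programme had reached those women.

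**Working it through.** The article gives no power calculation, effect size, standard deviation or contamination rate, so there is no figure of the plan to reproduce beyond 70 + 67 = 137, which agrees. The check is mainly a comparison of the passages.

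**1. Is there a route to control women?** The municipalities adjoin (2.2). The outreach has no stated geographic limit (3.4, Table 2). Table 3 does not bar control women from session 10, and handouts can be passed on. A route exists. Nothing shows how much it would be used.

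**2. Does it open before the later evaluations?** Session 10 closes the 10-week programme, so it comes before the 3- and 6-month evaluations. The promoter role belongs to the last stage in Table 2, but the article gives it no start date and does not defer it until follow-up ends. Control follow-up at 3 and 6 months is not stated arm by arm. It follows from 3.5, which repeats the same evaluation, with focus groups in both municipalities.

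**3. Would the data reveal it?** Knowledge, skills and diet are measured repeatedly in each arm, so a rise in control scores would be visible. Its cause would not be. Control women attend three sessions of their own, and the variables in 3.5 include nothing on contact with the 10-session programme.

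**4. Direction and illustrative size.** Let *c* be the share of control women reached and *e* the share of the effect that each takes up. Both are assumptions. With *s* = *c* × *e*, the expected observed difference is (1 − *s*) × the true difference. For example, *c* = 20% and *e* = 50% give *s* = 0.2 × 0.5 = 10%.

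For scale, take 67 and 70 women analysed as individuals, a two-sided 5% test and SD 1. The difference detectable with 80% power is (1.960 + 0.842) × √(1/67 + 1/70) = 2.802 × 0.1709 = 0.479 SD. Power under dilution is Φ(2.802 × (1 − *s*) − 1.960).

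| *s* (assumed) | Observed difference (SD) | Power |
|---|---|---|
| 0 | 0.479 | 80% |
| 10% | 0.431 | 71% |
| 20% | 0.383 | 61% |
| 30% | 0.335 | 50% |
| 50% | 0.239 | 29% |

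The last row is extreme: at *e* = 50% it needs every control woman to be reached. All the powers are best-case values, because they ignore that each arm is a single institution. The table shows sensitivity to *s*; it does not estimate *s*.

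**The case against.** The case on the other side has several sound parts.

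- **Outreach is an invitation.** Section 3.4 starts from the family, and separate institutions still prevent mixing within sessions. A reader might infer that the programme instructs women to spread its content and so cancels the safeguard. The text supports neither; it supports saying that the programme works against the safeguard.
- **Fading and catch-up can be separated.** A reader might infer that a narrowing gap could not be resolved into a fading effect and improving controls. It can: the first shows as falling intervention scores, the second as rising control scores. What remains unknown is why control scores rose.
- **Cross-arm acquaintance is not shown.** Close acquaintances recruited through one institution plausibly fall in the same arm as their contact, and the article describes social isolation as common among these women. A reader might take recruitment beyond the institutions' usual clientele as a measure of loose separation. It does not measure contact between arms, and 2.2 says that most participants are taking language classes at the institutions.
- **The full protocol may hold more.** Survey items are often left out of an article. But 3.5 does more than stay silent: it says the baseline variables are collected again with one named change. If the full survey already asks about exposure, that part of the point is met.
- **The size is assumed.** This stands in full.

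None of this removes the conflict between the stated reason for the allocation and an outreach component with no limit of place or time.

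**Conclusion.** The point holds as an internal conflict with an inexpensive remedy, and it is not a fatal flaw. Any spread to control women would bias the 3- and 6-month differences toward no effect. The end-of-sessions comparison is less exposed, though not immune, because handouts and session 10 precede it. The article gives no basis for estimating the amount; the illustrated fall from 80% power to between 71% and 50% assumes that controls take up 10% to 30% of the effect. Whether any control woman would be reached is unknown, and the evaluation as described would not show it. The conclusion rests on two readings: that both arms are evaluated at 3 and 6 months, and that outreach may begin by the end of the sessions. The text supports the first by implication and does not exclude the second.

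**What to change.** 1. **Table 3, session 10:** limit guests to people not enrolled in the control group.
2. **Section 3.5:** add two questions for control women at the end of sessions, 3 months and 6 months: whether they had contact with a woman attending the 10-session programme, and whether they received its booklets or recipes.
3. **Reporting:** give the share of control women exposed beside the 3- and 6-month results. Present any comparison without exposed controls only as a labelled sensitivity analysis, because exposure arises after allocation and dropping those women selects on it.
4. **Optional, section 3.4:** direct active outreach first to the woman's household and the intervention municipality until the control group's 6-month evaluation is complete. Informal talk cannot be policed, so this reduces spread without removing it.

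Items 1 to 3 cost some wording, two survey questions and a line of reporting. They should be settled before sessions begin, since exposure that was not recorded cannot be fully recovered later. Item 4 has a real cost, delayed outreach under aim (b), and the other changes do not depend on it.

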### 3.4. Phase 4: Implementation of the Food Education Intervention

In this phase, the food education intervention based on the Transtheoretical model [28] (Table 2) will be implemented. The participants from one entity will become the control group and from the other the intervention group.

The educational sessions will be done in small groups (12–15 women) to ensure the creation of positive dynamics and to create a trustworthy environment. There will be 6 subgroups of women for the intervention group and 5 subgroups for the control group. The intervention group will participate in 10 educative sessions for 10 weeks, while the control group will attend 3 sessions. Each weekly session will have a duration of 90 min.

Due to the linguistic barriers, the sessions will be carried out in Urdu and Punjabi by a plurilingual nutritionist. All the educational material will also be translated into Urdu. The learning outcomes related to educative sessions are summarized in Table 3. During the sessions, we will emphasize the following aspects:

Encourage healthy eating habits: Bearing in mind the cultural and linguistic aspects of participants healthy eating habits will be encouraged. We will combine the healthy characteristics of their traditional diet and combine them with innovative culinary techniques to facilitate the readoption. Apart from preparing the culturally and linguistically food adapted educational guides, we will also summarize and present some local guides such as “*Petits canvis per menjar millor* (small changes to eat better)” by the Public Health Agency of Catalonia [32] to enlighten the local guidance about health and nutrition.

Implement healthy eating behaviors: To implement the healthy eating behaviors the cooking skills of participants will be worked on. They will elaborate healthy snacks and healthy plates with the traditional ingredients and culinary techniques.

Adherence to the program: To actively engage the participants in the study, the sessions will be theoretical-practical. At the end of every session, there will be a final activity. We will also conduct three practical workshops about healthy snacks, food labels, and healthy plates. Throughout the sessions, we will keep providing personal counseling to those who needed.

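### One institution per arm: the arm effect cannot be separated from the institution, so the comparison cannot carry the randomised test of efficacy that the RCT label implies

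*Protocol article*

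**What the plan says.** **Label and aim.** Section 2.1 describes "community-based participatory research in which a RCT will be implemented", and the Abstract uses the same label. The first aim in the Introduction is to "evaluate the efficacy of a culturally and linguistically appropriate food education program based on the Transtheoretical Model of health behavior change".

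**Allocation.** Three places describe it. Section 2.2: "the participants from one institution will randomly become the control group and from the other, the intervention group". Abstract: "the participants from one municipality will randomly become the control group and from the other, the intervention group". Section 3.4: "The participants from one entity will become the control group and from the other the intervention group". Section 2.2 names the units as "Fundació Ateneu Sant Roc (Badalona) and Casa Àsia (Santa Coloma de Gramenet), two institutions working with the same goal". Casa Àsia contributes 70 women and Fundació Ateneu Sant Roc 67.

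**Reason given.** Section 2.2 chooses whole-institution allocation to prevent contamination. It supports comparability with three points: most women are learning the local languages at the institutions, the municipalities are neighbours with similar conditions, and all the women migrated between 2000 and 2022.

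**Delivery and measurement.** Sessions run in small groups: "There will be 6 subgroups of women for the intervention group and 5 subgroups for the control group". Section 3.5 collects the baseline variables again at the end of the sessions and repeats the evaluation at 3 and 6 months.

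**The concern.** The only random act is the choice of which of two institutions receives the 10-session programme. The session subgroups are formed inside an arm that is already assigned, so they are not randomised units and add no replication of the allocation.

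Any way in which the two institutions differ, or come to differ during follow-up, therefore coincides exactly with the intervention. Randomisation protects a comparison by spreading such differences over many units, and with one unit per arm nothing is spread. The RCT label tells readers and evidence syntheses that the between-arm comparison has this protection and that its p-values and confidence intervals reflect it. Here they would not, and this is the comparison on which the efficacy aim rests.

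**Working it through.** **Inputs from the article.** Two institutions, one per arm, with 70 and 67 women (section 2.2). The stated total reproduces: 70 + 67 = 137.

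**Input assumed.** The intraclass correlation (ICC) at institution level is not given. I take 0 to 0.05 as an illustrative range.

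**1. Separability.** Put an intercept, arm and institution in one model. The arm and institution columns are identical, so the matrix has rank 2 with 3 columns. Covariates measured on the women do not change this.

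**2. Degrees of freedom between sites.** With k sites per arm these are 2k − 2. For k = 1: 2 − 2 = 0, so between-site variance cannot be estimated.

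**3. Randomisation p-value.** The number of allocations is C(2k, k), and the smallest two-sided p-value is min(1, 2/C(2k, k)).

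| Sites per arm | Allocations | Smallest two-sided p |
|---|---|---|
| 1 (as planned) | 2 | 1.00 |
| 2 | 6 | 0.33 |
| 3 | 20 | 0.10 |
| 4 | 70 | 0.029 |

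A two-sided 5% randomisation test could first reject with four sites per arm.

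Steps 1 to 3 need no ICC.

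**4. Illustration of what ignoring site would do.** Take an unadjusted post-intervention comparison of the 137 women as if independent, with total variance 1.

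- Variance the test assumes: (1 − ICC)(1/70 + 1/67), where 1/70 + 1/67 = 0.0292.
- True variance: 2·ICC + (1 − ICC)(1/70 + 1/67).
- True type I error ≈ 2[1 − Φ(t/√ratio)], where t is the 97.5% point on 135 degrees of freedom and ratio is true variance over assumed variance.

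At ICC 0.01 the assumed variance is 0.99 × 0.0292 = 0.0289, the true variance is 0.0200 + 0.0289 = 0.0489, and the ratio is 1.69.

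| Assumed ICC | SE assumed | SE true | True type I error (formula) | Simulation, 100,000 runs |
|---|---|---|---|---|
| 0 | 0.171 | 0.171 | 4.8% | 5.1% |
| 0.005 | 0.170 | 0.198 | 8.8% | not run |
| 0.01 | 0.170 | 0.221 | 12.8% | 13.1% |
| 0.02 | 0.169 | 0.262 | 20.1% | 20.2% |
| 0.05 | 0.167 | 0.357 | 35.7% | 35.9% |

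(At ICC 0 the formula falls slightly below 5% because it sets a t critical value against a normal curve.)

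**5. More women per site would not help.** The true SE cannot fall below √(2·ICC): 0.14 SD at ICC 0.01 and 0.32 SD at ICC 0.05.

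**The case against.** **An effect can still be estimated.** A reader might infer that no intervention effect can be estimated at all. The document does not support that. Section 3.5 repeats the baseline variables, so a difference in change from baseline can be computed, and stable differences between the institutions cancel from it. This stands. What remains is the assumption that the two sites would have changed in parallel without the programme. With one baseline measurement and one site per arm, the data cannot test it.

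**Homogeneity.** The three points in section 2.2 are asserted before baseline data exist and without figures. A migration window of 22 years (2000 to 2022) is wide. None of the points covers site differences that arise during follow-up.

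**Contamination.** Avoiding it is a sound reason to allocate whole clusters. It is not a reason to have one cluster per arm.

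**Arm and municipality.** A reader might infer that these are the same variable. Only the Abstract words the allocation by municipality. Section 2.2 allocates by institution and invites close acquaintances, section 3.1 recruits in other community spaces, and Table 1 accepts residence in either municipality. Nothing says that every woman lives in the municipality of her institution. Arm equals institution is exact, and it is enough for the point.

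**Type I error figures.** It would be wrong to read them as this trial's error rate. They depend on an assumed ICC and on a test that the article does not specify. For change scores the relevant quantity is site-by-time variance, which may be smaller.

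**A later analysis plan.** A statistical analysis plan that is not shown may specify adjustment. It cannot create degrees of freedom between sites.

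**Conclusion.** The design is wrongly described as written. The allocation of two units is random, but there is no replication, so arm and institution are inseparable and the two-sided randomisation p-value is fixed at 1.0. These results follow from the stated design alone. The size of any bias is unknown: the article documents no actual difference between the institutions and gives no ICC. Standard errors that ignore site are too narrow whenever the ICC is above zero, and the illustrated error rates run from about 9% to 36% over assumed ICCs of 0.005 to 0.05. What the study can deliver is a two-site comparison of change from baseline whose causal reading rests on parallel trends. It cannot deliver a randomised test of efficacy.

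**What to change.** **Required.**

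- In the Abstract and section 2.1, replace 'RCT' with 'two-site controlled before-after study (one institution per arm)'.
- In section 2.2, state that the intervention effect cannot be separated from institution and that reading the result as an effect depends on parallel trends at the two sites.
- Analyse change from baseline.
- Present no p-value or confidence interval as a randomised test of efficacy, and read the efficacy aim in the Introduction within that limit.

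The cost is wording and a less favourable claim.

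**Option to consider before allocation, not required.** Randomising session subgroups within each institution would restore randomised replication. It carries a real contamination risk, which section 2.2 set out to avoid: most of the women attend language classes at the same institutions, and the programme asks them to pass its message on. The sponsor would have to weigh that dilution against the confounding with institution. The number of allocations this would offer cannot be read from section 3.4, which gives the 6 and 5 subgroups by arm. Six groups of at least 12 need 6 × 12 = 72 women, and the larger institution has 70.
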